# Study protocol: the SPInal NAVigation (SPINAV) trial – comparison of augmented reality surgical navigation, conventional image-guided navigation, and free-hand technique for pedicle screw placement in spinal deformity surgery

**DOI:** 10.1186/s12891-025-08817-3

**Published:** 2025-06-02

**Keywords:** Navigation, Spinal instrumentation, Pedicle screws, Augmented reality

## Abstract

**Background and purpose:**

Although navigation is increasingly used in spinal surgery, the advantage of different navigation technologies is still a matter of debate. Conventional image-guided navigation is currently the gold standard. However, modern, Augmented reality-based navigation methods are increasingly gaining ground. Surgical navigation in deformity surgery allows placement of pedicle screws in small and deformed pedicles and may result in both a higher accuracy and density of pedicle screw placement. The aim of this trial is to compare AR and conventional surgical navigation to free-hand technique.

**Patients and methods:**

This is a single center, open label, parallel assignment, three arm, randomized, controlled trial, comparing: Augmented reality surgical navigation (ARSN), Infrared surgical navigation (IRSN) and Free-hand (FH) technique. Individuals scheduled for spinal deformity surgery are eligible for inclusion. The inclusion criteria are written informed consent, age ≥ 12 years and spinal deformity. Subjects will be randomized intraoperatively and strictly sequentially.

**Outcomes:**

The primary endpoint is accurately placed pedicle screws based on intraoperative verification cone beam computed tomography (CBCT) scan. All radiological image analyses, on both intra- and postoperative imaging will be performed postoperatively by blinded reviewers.

Several secondary outcome measures including revision rate, radiation exposure, implant density and final accuracy will be analyzed. Patient reported outcomes will also be assessed. Finally, a cost–benefit analysis will be performed.

**Start of trial and estimated duration:**

The SPINAV trial started recruiting patients in January 2022 and will continue for approximately 2.5 years.

**Trial registration:**

The trial is registered at clinicaltrials.gov (NCT05107310) on 2021–11-03.

## Introduction

Spinal deformity constitutes a prevalent indication for surgery in childhood, with approximately 17 out of 100,000 individuals aged 0 to 18 undergoing spinal deformity surgery between 2015 and 2018, as indicated by a nationwide UK-based study [1]. Furthermore, the incidence of spinal deformity surgery is increasing in older adults, evident in a nationwide US registry reporting a noteworthy 141% surge in the utilization of long-construct fusions [2].

The complexity of spinal deformity surgery is underscored by its narrow error margins. Moreover, precise placement of pedicle screws and implants in severely deformed spines is particularly challenging. The pedicle's narrow dimensions magnify the importance of accuracy, as misplaced screws can lead to severe vascular, pulmonary, or neural injuries, along with compromised bone purchase [3].

While the reported accuracies of freehand pedicle screw placement in the thoracic and lumbar spine are highly variable, the benefits of improved accuracy, especially in the context of minimally invasive surgery, are evident.

Intraoperative fluoroscopy has been the traditional image guidance method for pedicle screw placement, offering a two-dimensional imaging perspective. The constant development of three-dimensional (3D) imaging technologies for intraoperative use has paved the way for surgical navigation within the field of spine surgery [4].

Computer-assisted navigation using intraoperative 3D imaging has been shown to improve screw placement accuracy, reduce complications due to screw misplacements, and consequently reduce the frequency of postoperative revision surgeries, when compared to conventional free-hand technique [5, 6].

In the context of spinal deformity surgery, previous reports have underscored enhanced accuracies when employing surgical navigation in scoliosis surgery, particularly in cases where anatomical intricacies pose heightened surgical challenges [7, 8].

Most of the commercially available navigation systems are based on infrared cameras, using outside-in detection of reflective spheres on a dynamic reference frame fixed to the patient’s spine. Emerging video-based systems incorporating augmented reality (AR) for surgical navigation, along with intraoperative three-dimensional imaging, represent innovative computer-assisted navigation techniques [9–11]. These systems have demonstrated relatively high accuracy, safety, and effectiveness in previous studies reports on pedicle screw placement [4, 12, 13].

Nonetheless, as of now, the majority of data in this area is based on retrospective and a few prospectively collected series [12, 14, 15], while randomized controlled trials on spinal deformity are lacking. This is similar to the current situation of evidence on robotic pedicle screw placement, where the evidence from randomized studies comparing robotic guidance to navigation is scarce [6, 16, 17].

The aim of this trial will hence be to compare conventional and AR surgical navigation to free-hand technique based on three main study domains: implant placement accuracy, intraoperative radiation exposure and metrics, and operative time for navigation. Intraoperative adverse events will also be reported. Finally, since data on cost-effectiveness is crucial to ensure adequate allocation of healthcare resources, the cost-effectiveness of this technology will be assessed.

## Methods and analysis

### Overview of study design

This is a single center open label parallel assignment three arm randomized controlled trial (Fig. 1). The trial will use a pragmatic approach and use existing equipment and document handling at the Karolinska University hospital and the existing quality registry for spine surgery, Swespine, for outcome assessments (www.swespine.se).

**Fig. 1 Fig1:**
[figure not shown]
Flowchart describing the study design

Study arms:Navigation group 1: Augmented reality surgical navigation (ARSN)Navigation group 2: Infrared surgical navigation (IRSN)Control group: Free hand (FH)

#### Study center and surgeon expertise

The Karolinska University Hospital is a publicly funded tertiary care center serving a region of approximately 2 million inhabitants. It is the region’s only spinal deformity center and handles all deformity surgeries in the region, with approximately 100 spine deformity surgeries being performed yearly. The study uses a pragmatic approach and use already available infrastructures, such as already existing navigation systems, hospital registries, radiology archiving and communications system, and the Swespine registry.

All surgeries were performed by senior orthopedic spine surgeons with at least 10 years of experience.

## Patient selection

### Subject enrollment

Individuals scheduled for spinal deformity surgery will be informed of the study at the time of an outpatient visit at the Karolinska University hospital.

Subject eligibility will be established before treatment randomization. Subjects will be randomized intraoperatively and strictly sequentially, as subjects are eligible for randomization. If a subject discontinues from the study, the subject number will not be reused, and the subject will not be allowed to re-enter the study. The inclusion will end when the sample size has been reached in both intervention arms.

### Inclusion criteria

• Written informed consent.

• Age 12 years and older.

• Spinal deformity surgery.

### Exclusion criteria

• Unable to give informed consent.

• Surgery without pedicle screws.

• Previous surgery with pedicle screws in the planned surgical area.

### Discontinuation and withdrawal of subjects

Subjects are free to discontinue their participation in the study at any time. This will not affect further treatment. Already collected study data for these patients will be kept in the study database, however new data, including data collected from registries will not be added.

### Premature termination of the study

The study group may decide to stop the trial or part of the trial at any time. In case of premature termination, the investigators will promptly inform the Ethics Committee and provide a detailed written explanation, which will be made publicly available.

### Randomization and blinding

The subjects are randomized in a 1:1 ratio, with stratification for operating theatre since the IRSN or ARSN system are located in different operating theatres. Randomization will take place intraoperatively after completed surgical exposure of the posterior elements and will be performed through the web-based platform of the Swespine registry using an allocation sequence hidden from the healthcare staff. Block randomization will be used. Block sizes will be unknown for the researchers.

The study design does not allow blinding of the surgeon. Since the primary outcome is assessed at the time of surgery and a short time thereafter, we do not find it necessary to blind the patient.

Intraoperatively, CBCT verification scans will be assessed by the surgeon to make decisions on screw revision. However, all radiological image analyses, on both intra- and postoperative imaging will be performed postoperatively by blinded reviewers.

Patient reported outcomes will however be assessed without influence of the care giver.

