### Study interventions and standard of care

#### Surgical treatment

All treatments involve surgical stabilization and fusion of the deformed spine. Additional surgical treatments for correction, such as osteotomies are performed as deemed by the treating surgeon.

All forms of treatment are available and used today at the Karolinska University hospital. The choice of supplier and brand of spine implants, as well as the use of intraoperative ARSN or IRSN are based on the preference of each surgeon. Neurophysiological monitoring is always performed as routine during spinal deformity surgery, with the exception of patients that are non-ambulatory. Motor evoked potential, sensory evoked potential and electromyography data will be collected to investigate any changes in neurophysiological parameters. Any deviations will be noted. Electromyography thresholds for all pedicle screws will be recorded.

Regardless of inclusion or randomization, patients will receive routine postoperative care including rehabilitation at the study center.

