### Study outcomes and variables

Primary and secondary study outcomes will be studied in comparisons between ARSN and free hand, IRSN and free hand, and ARSN and IRSN.

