## Discussion

We designed a randomized controlled trial, to compare free hand with navigation techniques in the placement of pedicle screws during spinal deformity surgery.

Despite a growing body of evidence endorsing the effectiveness of navigation techniques in the placement of pedicle screws, studies targeting the field of spinal deformity surgery are limited to small non-randomized and often retrospective series.

It is nonetheless in the field of deformity surgery where navigation technologies have demonstrated their most substantial impact on accuracy, particularly in neuromuscular scoliosis and the challenging terrain of the thoracic spine, where pedicles can be exceptionally small [31, 32]. Scoliosis may alter the anatomy of thoracic pedicles, posing a great challenge in spinal instrumentation [33].

To this day, retrospective studies reporting small differences in accuracy between FH and navigated techniques are often biased and lack robust matching protocols between cohorts. For instance, Noschenko et al. observed twice as many deformity cases in the navigation group compared to the freehand (FH) group [34]. This potentially explains the marginal difference in accuracy uncovered in that study, given the heightened complexity of deformity cases. Similarly, studies by Laudato et al. [35] and Shin et al. [36] demonstrated non-significant differences in accuracy but exhibited a larger proportion of screws in the thoracic spine in the navigation group compared to the FH group. Other prospective studies and recent meta-analyses of the literature have demonstrated similar results regarding the use of augmented-reality guidance [37, 38].

As a result, currently, the choice of techniques is mostly based on surgeon’s preference, and availability. This trial will be the first of its kind to address this topic in randomized and balanced cohorts of patients undergoing spinal deformity surgery with either navigation or FH techniques. Additionally, besides the planned trial, there are no studies addressing long-term quality of life outcomes in patients receiving pedicle screw placement with free hand versus navigation techniques.

Although intraoperative 3D imaging can increase the accuracy of pedicle screw placement, this technique may increase the total radiation exposure to staff and patients compared to standard fluoroscopy. We therefore aimed to study radiation exposure to both patients and surgical staff.

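### ARSN versus IRSN is listed beside the randomised contrasts, but on the natural reading of the allocation it is a non-randomised comparison between two theatres

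*Protocol article*

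**What the plan says.** In the protocol article:

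- Randomization and blinding sets an allocation of 1:1 and gives the reason for stratifying: "with stratification for operating theatre since the IRSN or ARSN system are located in different operating theatres". On timing it says: "Randomization will take place intraoperatively after completed surgical exposure of the posterior elements".
- Study outcomes and variables lists the planned contrasts in one sentence: "Primary and secondary study outcomes will be studied in comparisons between ARSN and free hand, IRSN and free hand, and ARSN and IRSN". The three contrasts stand on the same footing.
- Overview of study design, and the abstract, call the trial a three-arm randomised trial. The list of study arms under Fig. 1 has two navigation groups and one free-hand control group.
- Augmented reality surgical navigation uses the Philips Allura CBCT; Infrared surgical navigation uses the O-arm. Under Free hand, screws may be verified on either device.
- Sample size for primary objective plans about 22 patients in each group. Sample size for secondary objectives expects 44 navigated and 44 free-hand patients after pooling.
- Surgical treatment says that "the use of intraoperative ARSN or IRSN are based on the preference of each surgeon".

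**The concern.** A three-arm randomised trial gives three randomised pairwise contrasts only if every patient could have been drawn into any arm. Here the draw is made when the patient is already exposed in one theatre, and each theatre holds one navigation system. The only draw that can be carried out is that theatre's system or free hand. What decides between ARSN and IRSN is the theatre, and that is settled before randomisation by a process the article does not describe.

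Among navigated patients, system and theatre are therefore the same variable. Any difference between theatres in surgeons, case mix or imaging device is indistinguishable from a difference between systems. The device matters because the primary endpoint is graded on the intraoperative verification CBCT. A reader who sees ARSN versus IRSN in the list of primary-outcome comparisons of a randomised trial will take the result as randomised evidence on which system is more accurate.

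**Working it through.** **1. The plan's own figure.** Inputs from Sample size for primary objective: 91% navigated, 84% free hand, one-sided alpha 0.05, power 80%, continuity correction.

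- Uncorrected: n = [1.645·√(2·0.875·0.125) + 0.842·√(0.84·0.16 + 0.91·0.09)]² / 0.07² ≈ 275 screws per group.
- Corrected: (275/4)·[1 + √(1 + 4/(275·0.07))]² ≈ 303, close to the stated 301.
- 301 × 1.10 = 331.1, rounded up to 332; 332/15 = 22.1, so about 22 patients per group.

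The arithmetic is sound, but it covers navigated versus free hand only. Both systems are assumed to reach 91%, so no effect is specified for ARSN versus IRSN.

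**2. Which design fits the patient counts?**

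- Three arms of 22: 3 × 22 = 66 patients, of whom 22 are free hand.
- Two theatres, each 22 navigated + 22 free hand: 2 × (22 + 22) = 88 patients, of whom 44 are navigated and 44 free hand.

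Only the second gives the 44 and 44 stated for the secondary objectives. It also fits a 1:1 rather than 1:1:1 ratio, and free-hand verification on either CBCT device.

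**3. What each contrast carries.** Let d be the difference in accuracy between theatres for reasons other than technique.

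| Contrast | Share of d that enters |
|---|---|
| ARSN vs FH, or IRSN vs FH, same theatre | 0 |
| Both systems pooled vs all FH (44 vs 44), balanced by theatre | 0 |
| One system vs FH from both theatres in equal parts, if that were done | d/2 |
| ARSN vs IRSN | d |

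**4. Illustration of size.** The documents give no d, so a range is assumed. Further assumptions: no technique effect, mean accuracy 87.5%, 330 screws (22 × 15) per cell, independent screws, normal approximation.

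For d = 3 points (89% vs 86%), the null standard error is √(0.875·0.125·2/330) = 0.0257, so the two-sided critical difference is 1.96 × 0.0257 = 0.0505. The standard error under the two rates is √((0.89·0.11 + 0.86·0.14)/330) = 0.0257. The chance of exceeding the critical value is 1 − Φ((0.0505 − 0.03)/0.0257) ≈ 0.21, and the opposite tail adds about 0.001.

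| d (points) | Two-sided false-positive rate, ARSN vs IRSN |
|---|---|
| 0 | 5% |
| 2 | 12% |
| 3 | 21% |
| 5 | 49% |

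If one system were tested against free-hand patients from both theatres (330 vs 660 screws), the bias would be 1, 1.5 or 2.5 points at d = 2, 3 or 5. The one-sided rate for the system in the better theatre would be about 11%, 16% or 31%.

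**5. Cost in precision of respecting the strata.** At 91% vs 84% with 330 vs 330 screws, a same-theatre contrast has about 86% one-sided power (78% two-sided). An indirect ARSN−IRSN contrast, the difference of the two within-theatre differences, has SE = √2 × √((0.91·0.09 + 0.84·0.16)/330) = √2 × 0.0256 = 0.0362, a 95% half-width of 7.1 points. The direct contrast has SE = √(2·0.0819/330) = 0.0223, half-width 4.4 points, but that interval ignores d. All of these are before any allowance for clustering of about 15 screws within each patient.

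**The case against.** Several points on the other side stand.

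- **The main aim is not affected.** The abstract and introduction set out to compare the two navigation methods with free hand, and only that is powered. Within a theatre those contrasts are properly randomised, and late, concealed allocation is a strength for them. ARSN versus IRSN has no power calculation and no equivalence or non-inferiority claim attached.
- **Confounded free-hand controls.** A reader might infer from the single control group and the unadjusted tests under Statistical analysis that each system will be compared with free-hand patients from both theatres. The article does not say so. It sizes equal groups of about 22, which is what a same-theatre comparison gives, and the only pooling it describes (44 vs 44) is balanced by theatre. Adjustment for a stratification factor is commonly left to an analysis plan, which is not shown. The d/2 bias is therefore conditional.
- **Surgeon preference.** A reader might infer that surgeons choose the theatre and hence the system. The sentence under Surgical treatment does not mention theatre, also covers implant brand, and can be read as describing routine practice. What can be said is that random assignment to theatre is not described.
- **Balanced cohorts.** The Discussion's promise of randomised and balanced cohorts refers to navigation versus free hand, which this design delivers. It is not a claim about ARSN versus IRSN.

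None of this rescues ARSN versus IRSN. An analysis plan could add theatre to the model for the free-hand contrasts, but among navigated patients theatre and system coincide, so no adjustment can separate them or make that contrast randomised.

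**Conclusion.** The concern holds for ARSN versus IRSN. On the natural reading of the allocation text, supported by the 44 and 44 patient counts, the trial is two theatre-specific 1:1 randomisations. ARSN versus IRSN is then a between-theatre comparison that carries the whole of any theatre, surgeon, case-mix and device difference. It should not stand unmarked beside the randomised contrasts.

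The size is unknown because the documents give no theatre difference. The 12%, 21% and 49% are illustrations at assumed differences of 2, 3 and 5 points with independent screws; the bias itself equals d whatever is assumed about clustering. Comparison of one system with free-hand patients from both theatres would import about half of d, but the article neither states nor excludes it. Pooled navigation versus pooled free hand is not confounded by theatre.

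**What to change.** 1. Describe the trial as two theatre-specific 1:1 randomised comparisons, ARSN vs FH and IRSN vs FH, and state how patients come to be assigned to a theatre.
2. Reconcile the three-arm label and about 22 patients per group with 44 free-hand patients. This affects power: if free hand were only 22 patients in all (11 per theatre, 165 screws), a same-theatre contrast of 330 vs 165 screws would have about 73% one-sided power instead of 86%.
3. State that each system is compared with free-hand patients randomised in the same theatre, or that the analysis is stratified by theatre.
4. Label ARSN versus IRSN as non-randomised and exploratory wherever it is listed. If the indirect contrast is reported, give its confidence interval and state its assumption: theatre, surgeon and case-mix effects are additive and equal for navigated and free-hand screws. That assumption is doubtful if surgeons work with a system they prefer.

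The cost is wording and one model term, since theatre is already the stratification factor. The downside is a wider interval for ARSN versus IRSN (about 7.1 rather than 4.4 points either side, before clustering) and no borrowing of free-hand controls across theatres.

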### Study interventions and standard of care

#### Surgical treatment

All treatments involve surgical stabilization and fusion of the deformed spine. Additional surgical treatments for correction, such as osteotomies are performed as deemed by the treating surgeon.

All forms of treatment are available and used today at the Karolinska University hospital. The choice of supplier and brand of spine implants, as well as the use of intraoperative ARSN or IRSN are based on the preference of each surgeon. Neurophysiological monitoring is always performed as routine during spinal deformity surgery, with the exception of patients that are non-ambulatory. Motor evoked potential, sensory evoked potential and electromyography data will be collected to investigate any changes in neurophysiological parameters. Any deviations will be noted. Electromyography thresholds for all pedicle screws will be recorded.

Regardless of inclusion or randomization, patients will receive routine postoperative care including rehabilitation at the study center.

#### Augmented reality surgical navigation

After standard exposure of the region of interest of the spine a cone beam CT (CBCT) (Philips Allura, Philips, Best, The Netherlands) of the area is performed. Navigation is based on the recognition of optical markers (fiducials) on the skin by the equipment during the CBCT and navigation [12, 18, 19]. The CBCT will result in a three-dimensional image of the spine in which screws are placed virtually on a computer screen. Navigation then takes place. The navigation will show the entry point and direction of the planned screws on an augmented reality image screen in the operating theatre [14, 20, 21]. After placement of the screws, the positioning is checked with a second CBCT. Misplaced screws may be repositioned or extracted.

After screw placement, rods are placed, correction of the deformity and fusion are performed, and the wound is closed.

